### Interventions

The BVA group will be treated with a bee venom (BV) increment protocol of six sessions over three weeks. The NSAIDs group will be prescribed loxoprofen (loxonin, 60 mg/Tab, Dong Wha Pharm Co., Ltd, Seoul, Korea), at a dose of one tablet administered orally three times per day over three weeks. The combined treatment group will be treated according to the BV increment protocol and will be prescribed loxoprofen over three weeks.

### Bee venom acupuncture

BVA will be prepared as dried bee venom powder (Yoomil Garden, Hwasun, Korea), diluted (1:20,000) and filtered in normal saline (0.9% NaCl) at the Korean medical pharmacy at KHUHGD. BVA treatment will be conducted using 26-gauge sterile disposable syringes (Green Cross Co., Yongin, Korea) containing bee venom diluted with normal saline (0.9% NaCl).

After sterile skin preparation, participants will be administered a perpendicular, subcutaneous injection at a depth of 0.5 to 1.0 cm with the patient lying in the prone position. The acupuncturist will treat participants under the predefined BVA protocol at predefined acupoints. BVA intervention will consist of six sessions twice a week for three weeks, under the following weekly BVA incremental protocol: 0.2 ml for the first week, 0.4 ml for the second week and 0.8 ml for the third week. The predefined points (SI12, SI14, BL11, BL12, TE15 and GB21) have been carefully selected from textbooks and research articles by a process of consensus among participating Korean medical doctors (KMD), all of whom are experienced in the treatment of chronic neck pain.

### Allowance of concurrent treatment of patients

During the study period, all other interventions, drugs and treatments for neck pain will be prohibited including surgical procedures, injections, acupuncture, physical therapy or the use of muscle relaxants, narcotics and analgesics. Regular medications not intended to affect neck-pain related dysfunction will be allowed. Any change in concurrent treatment will be recorded at every visit.

### Outcomes

Assessment of neck pain-related dysfunction, pain and quality of life will be collected five times over eight weeks: at screening, visit two (baseline), four, six, eight (4th week assessment) and nine (8th week assessment) follow-up sessions. Medical history and sociodemographic characteristics, including age, gender, marital status, residence, occupation and education level will be taken from the screening visit. Any unpredicted, adverse events will be recorded at each visit (Table 1).

**Table 1 T1:** Schedule for data collection: outcome measures per visits

**Measures**	**Screening**	**Visit 2 (baseline)**	**Visit 4**	**Visit 6**	**Visit 8 (4th week assessment)**	**Visit 9 (8th week assessment)**
Sociodemographic characteristics	○					
Physical examination	○					○
Laboratory tests	○				○	
VAS for bothersomenesst of CNP	○	○	○	○	○	○
VAS for pain intensity of CNP	○	○	○	○	○	○
Neck disability index		○	○	○	○	○
EuroQol 5-Dimension		○	○	○	○	○
Beck’s depression inventory		○			○	○
SF-36		○			○	○
‘Skin roll’ test		○			○	○
Credibility test		○			○	
Adverse experiences*		○	○	○	○	○

*Adverse experiences will be monitored throughout the clinical trial.

CNP: chronic neck pain; VAS: visual analogue scale.

### Primary outcome measurement

bothersomeness of chronic neck pain will be evaluated using the 10 cm visual analog scale (VAS) for CNP. Participants will be asked to report the degree of clinical severity and impact on activities of daily life experienced within the past week on a continuous discomfort scale of 0 to 10 (0, absence of discomfort; 10, the worst discomfort imaginable) [24] at screening, visit two (baseline), four, six, eight (4th week assessment) and nine (8th week assessment) follow-up sessions. The primary end point will be the VAS score at the four-week follow-up, one week after the completion of the three-week treatment session.

### Secondary outcome measurements

#### VAS for pain intensity

Pain intensity of CNP will be assessed using a 10 cm VAS, a fast and straightforward method for evaluating the subjective degree of pain intensity [25]. Participants will be asked to report the degree of pain intensity using the 10 cm VAS (0, absence of pain; 10, the worst pain imaginable) at screening, visit two (baseline), four, six, eight (4th week assessment) and nine (8th week assessment) follow-up sessions.

#### The neck disability index (NDI)

Neck pain-related dysfunction will be assessed using the validated Korean version of NDI [26] at visit two (baseline), four, six, eight (4th week assessment) and nine (8th week assessment) follow-up sessions. The NDI contains 10 questions about pain intensity, personal care, lifting, reading, headaches, concentration, work, driving, sleeping and recreation. Each question is rated using a 6-point scale from 0 to 5 points (0, absence of problem; 5, disabled by neck pain).

#### The EuroQol 5-dimension

Quality of life (QOL) for patients with CNP will be assessed using the Korean version of the EuroQol 5-dimension (EQ-5D) [27,28] at visit two (baseline), four, six, eight (4th week assessment) and nine (8th week assessment) follow-up sessions. The EQ-5D contains five questions regarding mobility, personal care, daily activities, pain/discomfort and anxiety/depression. Each question is rated on a scale from 1 to 3 points (1, better state of health; 3, worse state of health).

#### Beck’s depression inventory

The depressive status for patients with CNP will be assessed using the Korean version of Beck’s Depression Inventory (BDI) [29,30] at visit two (baseline), eight (4th week assessment) and nine (8th week assessment) follow-up sessions. The BDI contains 21 questions about depressive symptoms rated from 0 to 3 points (the lower the score, the lower the depressive state).

#### SF-36

Health-related QOL for patients with CNP will be assessed using the Korean version of the Medical Outcome Study Short-form 36-Item Health Survey (SF-36) [31,32] at visit two (baseline), eight (4th week assessment) and nine (8th week assessment) follow-up sessions. The SF-36 tests the correlation between health-related QOL and related factors (sex, age, physical function and functioning of daily life) rated on a 5-point scale (1, best status; 5, worst status).

#### Credibility test

The credibility of BVA treatments will be assessed using the credibility test [33] at visit two (baseline) and eight (4th week assessment) follow-up sessions. Participants will rate the credibility of the treatment by answering four questions regarding improvement expected, recommendation to others, rationality of treatment and effectiveness expected for other diseases on a numeric rating scale, with 0 as not at all and 6 as maximal agreement.

#### ‘Skin roll’ test

Painful intervertebral dysfunction will be assessed using the ‘skin roll’ test [34,35] at visit two (baseline), eight (4th week assessment) and nine (8th week assessment) follow-up sessions. The ‘skin roll’ test will be analyzed by an averaging of each of two measured values by two independent assessors: 1) the skin fold thickness measured using a Harpenden skinfold caliper (Baty International, Burgess Hill, United Kingdom); 2) the pain intensity elicited by pressure using a baseline dolorimeter (Fabrication Enterprises. Inc., White Plains, United States); and 3) the subjective pain intensity scored by the VAS.

### Safety

All adverse events and vital signs will be observed and reported according to the standard operating protocol (SOP) of the KHUHGD IRB. Liver and renal functions of each participant will be assessed before the treatment and one week after the end of treatment. A pregnancy test will be performed for female participants of childbearing age at any time required.

### Sample size

Although there are previous researches on the effect of BVA and NSAIDs on chronic neck pain, there are insufficient data to estimate the clinical meaningful minimal change of the combined treatment of BVA and NSAIDs. This study is designed to provide the clinical evidence to estimate the sample size required for a full-scale RCT. As a pilot trial, we will recruit 60 patients into three parallel groups (BVA, NSAIDs or combined treatment). We will assess the impact of the interventions and the safety of combined treatment of different interventions on a limited number of patients.

### Randomization and allocation concealment

A total of 60 participants will be randomly assigned following simple randomization procedures, with a 1:1:1 allocation ratio. The randomization sequence will be generated by an independent researcher using a computerized, random-number generator through a Microsoft Office Excel 2007 software package. Opaque envelopes labeled by study patient number will be conveyed to the interviewer (CRC). The CRC will open the sealed envelopes and allocate participants into the predefined treatment arms. Allocation concealment will not be broken until the completion of the study. The random allocation assignment will be performed only after a participant is confirmed to be eligible and written informed consent has been obtained. Detailed information, including the treatment arm and randomization number from an individual participant will be recorded in the case report form (CRF) and randomization table.

### Blinding

As assessor-blind RCT, the researcher performing the outcome measure assessment will be blinded to each patients’ treatment allocation and will be prohibited from taking part in any conversation about the treatment procedures. It is not possible to conceal BVA practitioners to patient allocations. BVA practitioners will be prohibited from any conversations other than those regarding BVA treatment. NSAIDs will be prescribed by another researcher who will be blinded to the patient allocations and will not be allowed to take part in any conversation regarding the patients' condition. Participants will receive their medication at the KHUHGD pharmacy. Pharmacists will be blinded to the patient allocations and will only be allowed to provide general information regarding medication administration. Statistical analysis will be performed by an independent statistician who will be blinded to patient allocation. All researchers will undergo training prior to participation in this study.

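### The unblinded BVA practitioners' conversation rule limits topic but not content, leaving an avoidable, unequal source of expectation bias in the two contrasts against NSAIDs

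*Protocol article*

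**What the plan says.** The Blinding section of the protocol article gives each role its own limit.

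- **BVA practitioners.** They know the allocation: "It is not possible to conceal BVA practitioners to patient allocations". Their limit is: "BVA practitioners will be prohibited from any conversations other than those regarding BVA treatment".
- **NSAID prescriber.** This researcher is described as blinded and "will not be allowed to take part in any conversation regarding the patients' condition".
- **Pharmacists.** "Pharmacists will be blinded to the patient allocations and will only be allowed to provide general information regarding medication administration".
- **Outcome assessor.** Blinded, and kept out of conversations about the treatment procedures.

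On contact, the section Bee venom acupuncture states: "BVA intervention will consist of six sessions twice a week for three weeks". The combined group follows the same injection protocol. No comparable series of practitioner contacts is described for the NSAIDs group.

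On the outcome, the section Primary outcome measurement makes the VAS the patient's own rating: "Participants will be asked to report the degree of clinical severity and impact on activities of daily life experienced within the past week". Its timing is: "The primary end point will be the VAS score at the four-week follow-up, one week after the completion of the three-week treatment session".

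The article names assessors and statisticians as blinded. It does not list participants and describes no sham injection or placebo tablet.

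**The concern.** Conversation limits of this kind exist to contain bias when treatment is open. Here the staff who know the allocation, and who meet patients most often, are limited only in what they talk about, and that topic is the treatment under test. As worded, a remark that bee venom usually helps would comply with the rule. A pharmacist who said the same of loxoprofen would break theirs.

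The outcome is self-rated, so a patient whose hopes have been raised may report less bothersomeness at week 4 whatever the treatment has done. The shift would favour the BVA-containing arms in both comparisons with NSAIDs. The Background section wants a preliminary look at non-inferiority of BVA to NSAIDs, and a shift of this kind makes that conclusion easier to reach. The Discussion also says the findings may be used to calculate an effect size for the full-scale trial, so a biased contrast could carry into its planning. Baseline-adjusted ANCOVA does not remove a bias that arises after randomization.

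**Working it through.** The plan gives no figure to reproduce: the Sample size section sets 60 patients as a pilot number without a power calculation. The main check is therefore a comparison of the rules.

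**Step 1: the rules side by side**

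| Role | Knows allocation? | Limit stated | Is talk of expected benefit excluded? |
|---|---|---|---|
| BVA practitioner | Yes | Topic: BVA treatment | No |
| NSAID prescriber | Stated blinded | Not the patient's condition | Not expressly |
| Pharmacist | Stated blinded | Content: general administration information | Yes |

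Only the pharmacists have a limit on content. The practitioners have a limit on topic, and expected benefit falls within that topic.

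**Step 2: which contrasts are exposed**

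- BVA versus NSAIDs: one arm has six practitioner sessions and the other has none. Exposed.
- Combined versus NSAIDs: both arms meet the prescriber and pharmacist, and only the combined arm meets the practitioners. Exposed.
- Combined versus BVA: both arms meet the practitioners under the same rule. Largely unaffected.

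**Step 3: what a shift would do, for scale only**

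From the article: 60 patients at 1:1:1, so 60/3 = 20 per arm (simple randomization does not guarantee this), and a significance level of 0.05. Assumed: a two-sided test, no true difference, and an expectation shift of s standard deviations. The shift is not a document figure, so a range is shown.

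Standard error of a contrast between two arms = sqrt(2/20) = 0.316 SD.

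Rejection rate = 1 − Φ(1.96 − s/0.316) + Φ(−1.96 − s/0.316).

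| Assumed shift s | s/0.316 | Rejection rate |
|---|---|---|
| 0 | 0 | 5.0% |
| 0.1 SD | 0.32 | 6.2% |
| 0.2 SD | 0.63 | 9.7% |
| 0.3 SD | 0.95 | 15.8% |

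A noncentral t calculation on 38 degrees of freedom, in centimetres and with an assumed SD of 1.5 to 2.5 cm, agrees. A shift of 0.3 cm gives 9.5% down to 6.6%, and a shift of 0.5 cm gives 17.7% down to 9.5%, as the SD rises.

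These rates describe a total expectation difference between arms from any cause. They do not measure what this one sentence contributes.

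**The case against.** **The sentence is a restriction and never mentions benefit.** This is true. Practitioners must be able to talk about an injected treatment, and the sentence narrows their talk to it. A reader might infer that the plan endorses expectation-raising talk, and the text does not support that. What stands is narrower: such talk is not excluded, whereas the pharmacists' rule excludes it.

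**The NSAIDs side is not closed either.** A reader might infer that talk of benefit is allowed in two arms and forbidden in the third. The article does not say so. The prescriber is barred from discussing the patient's condition, and nothing expressly bars talk about loxoprofen. The rules are unequal, but not as cleanly as permitted against forbidden. A fix aimed only at the acupuncturists would leave this gap.

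**Expectation would differ anyway.** Patients know their treatment, and the BVA arms have six hands-on sessions. This stands. A reader might credit a whole shift of 0.2 or 0.3 SD to the conversation rule, and nothing in the article supports that.

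**A script may sit in a fuller document.** It may. The article describes customized training, and its list of contents is only illustrative. The absence of a script is therefore not the point. The point is the rule the article does state, which fixes a content limit for one role and only a topic limit for another.

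**The setting is pragmatic.** The Discussion wants treatment as in usual practice, where practitioners talk freely. But the Blinding section already restricts talk for every role, so the sponsor has chosen control here.

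**Expectation is measured.** The credibility test, at visits 2 and 8, includes expected improvement. As described it concerns BVA treatments, so it offers partial insight and no clear comparison with the NSAIDs arm.

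**Conclusion.** The point holds as a minor one. The rule for the unblinded practitioners does not exclude talk of expected benefit over six sessions, and the other treating staff work under different limits, of which only the pharmacists' is a content limit. With a self-rated primary VAS and patients who know their treatment, this is an avoidable and unequal source of expectation bias in BVA versus NSAIDs and combined versus NSAIDs. Combined versus BVA is largely unaffected.

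The size is unknown. Bias is possible under the rule, not demonstrated, and it would add to open-label expectation that no conversation rule removes. The conclusion rests on reading the sentence as written and on patients knowing their treatment, which follows from the absence of any described sham or placebo.

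Severity is limited by the pilot purpose: the Planned statistical analysis section treats hypothesis tests as preliminary. The point still deserves a change because the pilot is meant to refine the protocol and inform the effect size for the full-scale trial.

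**What to change.** In the Blinding section, replace the separate limits on BVA practitioners, the NSAID prescriber and pharmacists with one rule for all three. Suggested wording:

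*All treating staff will give procedural and administration information only. They will make no statement on expected benefit and no comparison between treatment arms. Reports of adverse events will always be taken.*

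Cover the rule in the training already planned for all researchers (Blinding) and for the two acupuncturists (Education of acupuncturists). Applying it to the prescriber as well avoids creating an imbalance in the other direction.

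The cost is a short change of wording and a brief addition to existing training. The downside is slightly less natural talk than in the usual practice the Discussion aims to reflect. The change removes only the avoidable part of the problem; expectation from open treatment and unequal contact remains and should be acknowledged when the two NSAIDs contrasts are interpreted.

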### Education of acupuncturists

Two licensed KMDs who specialize in acupuncture and moxibustion will be designated as the BVA treatment practitioners and will take educational courses to ensure their strict adherence to the study protocol and to become familiar with administering study treatments. In order to ensure consistency in the BVA treatment, the two acupuncturists will undergo intensive and customized training for a full understanding of the BVA increment protocol, including details such as acupuncture points and weekly bee venom dose increments.

### Withdrawal and dropout

Participation in the study will end at any stage if the patient refuses to continue, withdraws consent, violates inclusion or exclusion criteria or the trial protocol, or completes less than four treatment sessions as determined by the attending KMD researchers. The trial will be stopped if the principle investigator believes that there are unacceptable risks of serious adverse events. No interim analysis will be conducted.

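### The withdrawal rule ends study participation, not only treatment, for protocol violation or fewer than four sessions, so week-4 and week-8 outcomes can be lost after randomisation for reasons linked to response

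*Protocol article*

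**What the plan says.** The rule in Withdrawal and dropout opens with "Participation in the study will end at any stage if the patient refuses to continue". The same sentence, with the same consequence, covers withdrawn consent and a patient who "violates inclusion or exclusion criteria or the trial protocol, or completes less than four treatment sessions as determined by the attending KMD researchers". What ends is participation in the study. The article nowhere separates this from stopping treatment, and describes no visit or assessment after removal.

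Four other places bear on it:

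- **Allowance of concurrent treatment of patients:** "During the study period, all other interventions, drugs and treatments for neck pain will be prohibited". The list that follows includes analgesics, so taking one for neck pain breaches the protocol.
- **Interventions and Bee venom acupuncture:** "BVA intervention will consist of six sessions twice a week for three weeks". The NSAIDs arm takes tablets for three weeks, and no sessions are described for it.
- **Blinding:** "It is not possible to conceal BVA practitioners to patient allocations". Education of acupuncturists says that these practitioners are two licensed Korean medical doctors (KMDs).
- **Randomization and Primary outcome measurement:** allocation follows confirmed eligibility and consent, and the primary end point is the bothersomeness VAS at week 4, a week after treatment ends.

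**The concern.** A patient who breaches the protocol or attends poorly has already been randomised. Ending that patient's participation removes the week-4 and week-8 outcomes from the comparison. The reasons need not be neutral: poor relief can lead a patient to take a prohibited analgesic, and poor relief or a local reaction can lead one to stop attending. The patients left in each arm are then no longer the groups that randomisation formed. ANCOVA adjusts for baseline characteristics, not for what happened after baseline, so it cannot be relied on to restore the comparison.

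The article says its findings can be used to calculate the effect size for a full-scale trial, so a distorted estimate would carry forward. Safety is affected too: the liver and renal tests planned for a week after treatment could be missed by patients already removed.

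This is not a complaint about an undefined analysis set, which an analysis plan could supply. The rule stops data collection, and no later plan can recover outcomes that were never measured.

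**Working it through.** The plan gives no effect size, SD, power or dropout rate to reproduce; 60 is set as a pilot size. The check therefore takes the text first, and then an illustration on stated assumptions.

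**1. Can removal come before the primary outcome?** The schedule is 2 sessions × 3 weeks = 6, and the threshold of 4 is 4/6 = 67% of them. A patient who misses a third session can complete at most 6 − 3 = 3 (assuming missed sessions are not made up) and so falls below four. That can happen from the third session (week 2) to the sixth (week 3), in every case before week 4. A protocol violation can occur at any time.

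**2. Does the rule act equally in all arms?** The protocol-violation trigger applies to all three. The session trigger has a defined meaning only in the BVA and combined arms. For the NSAIDs arm the text is open: Participants says that the coordinator schedules treatment sessions after allocation, without limiting this to BVA. The BVA and combined arms share the same six sessions, so this possible asymmetry does not arise in the contrast between them.

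**3. Who decides?** The attending KMD researchers do. The only treating KMDs described are the two BVA practitioners, who know the allocation, but the article does not say that they are the same people. The phrase giving them the decision may also govern the session count alone.

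**4. Illustrative size.** Let f be the share removed from an arm and d how much worse (cm on the VAS) the removed patients are than those retained.

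- Mean of all randomised = (1 − f) × retained mean + f × removed mean = retained mean + f × d. The shift from analysing only the retained is therefore f × d.
- Assumed f = 0.10 to 0.30 and d = 1 to 2 cm, with no loss in the comparator: 0.10 × 1 = 0.1 cm to 0.30 × 2 = 0.6 cm.
- With loss in both arms the net shift is f₁d₁ − f₂d₂. Equal losses with equal gaps cancel. Loss only in the other arm reverses the sign, to −0.1 to −0.6 cm. If those who skip sessions are early improvers, d is negative and the sign reverses again.

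**5. Comparison with precision.** Assume 20 per arm, SD 2 cm, baseline correlation 0.5, and 60 − 3 − 1 = 56 residual degrees of freedom. The 95% half-width for a pairwise contrast is t(0.975, 56) × 2 × √(1 − 0.25) × √(2/20) = 2.003 × 1.732 × 0.316 = 1.10 cm. The shift is 0.1/1.10 = 9% to 0.6/1.10 = 55% of that.

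**6. Effect on a nominal 5% test.** Same assumptions in SD units (d = 0.5 to 1.0 SD), unadjusted comparison, normal approximation, SE = √(1/20 + 1/(20(1 − f))):

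| Share removed from one arm | n | Bias (SD) | Type I error |
|---|---|---|---|
| 0% | 20 vs 20 | 0 | 0.050 |
| 10% | 18 vs 20 | 0.05 to 0.10 | 0.053 to 0.061 |
| 20% | 16 vs 20 | 0.10 to 0.20 | 0.060 to 0.092 |
| 30% | 14 vs 20 | 0.15 to 0.30 | 0.072 to 0.138 |

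**The case against.** The strongest reply is that three tempting extensions go beyond the text, and on each the reply is right.

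- **That the arms certainly lose outcomes unequally.** A reader might infer this because sessions are defined only for BVA. But scheduled treatment sessions are mentioned for participants generally, and Table 1 gives one visit schedule for all arms, so NSAIDs visits might count. Unequal loss is possible, not established.
- **That unblinded staff decide.** The attending KMD researchers are never equated with the BVA practitioners, and a count below four leaves little room for discretion.
- **That the bias favours BVA.** The ban on other neck-pain treatment acts in every arm. Removing NSAIDs patients who took another analgesic would flatter that arm, and early improvers who skip BVA sessions would push the other way. The net sign is unknown.

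Further points limit the weight. Removed patients can still be counted as a feasibility result. Nothing tells anyone to discard data already collected, and the VAS is also taken at visits 4 and 6. This is a pilot whose tests are to be read cautiously. Even the upper illustrative shift is about half the half-width.

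What survives is the core: participation ends, and no later assessment is provided for. Earlier VAS values could support a missing-data method, but only on assumptions about the unobserved week-4 values that could not be checked. Cautious reading of tests does not protect an effect estimate meant to inform the next trial.

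**Conclusion.** The point holds on the text. As written, the rule ends follow-up of randomised patients for reasons that can depend on response, and can do so before the primary outcome is measured. Differential loss between arms and a decision by unblinded staff are possibilities that the wording leaves open, not facts that it states.

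Neither the direction nor the size of the bias can be derived from the documents. The 0.1 to 0.6 cm range, set against a half-width of about 1.1 cm, rests wholly on assumed removal rates, outcome gap, SD and correlation, and on no loss in the comparator. It shows that the effect could range from negligible to about half the half-width. The case for changing the rule is that outcomes never collected cannot be recovered by analysis, while collecting them costs little.

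**What to change.** Amend Withdrawal and dropout to treat stopping study treatment and ending follow-up as two separate events:

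- Low attendance or a protocol violation does not end follow-up. Only withdrawn consent or refusal of further assessment does.
- Collect the scheduled visit 8 and 9 outcomes and safety data for all other randomised patients, and include them in the arm to which they were randomised.
- Use the four-session threshold only to describe adherence or to define a supportive per-protocol set, and state how it applies to the NSAIDs arm.

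When treatment itself stops is left to the clinicians.

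The cost is one amended paragraph and a few follow-up contacts, at visits already in Table 1, with patients who have stopped treatment. There is one limit: Trial status gives a start in July 2013 and expected completion in July 2014, and the article is dated April 2014, so patients already removed may not be recoverable. Their number, arm and reason for removal should be reported.
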